### Participant timeline {13}

The participant timeline is listed in Table 2.

**Table 2 Tab2:**
[figure not shown]
The participant timeline of our study

Note: T1*, immediately after the first or second dose of NCV; T2*, 3 days after the first or second dose of the NCV; T3*, 5 days after the first or second dose of NCV; T4*, 7 days after the first or second dose of NCV; T5*, 14 days after the first or second dose of NCV; #, record as cases with visual analogue scale (VAS) scores from 0 to 10; Adverse events of the interventions*, including abnormal pain, skin allergy, and other adverse reactions

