## Introduction

### Background and rationale {6a}

As of October 5, 2021, a total of 234 million people were confirmed infected with SARS-CoV-2, including 4.8 million deaths worldwide [1]. Developing immunity through COVID-19 vaccination provides a reduced risk of being infected and helps to fight the virus if exposed, which can save uncounted lives and give us a pathway out of the global disaster [2, 3]. Researches showed that novel coronavirus-19 vaccines (NCV) were of considerable efficacy, and improvement on efficacy, especially long-term protection, and exploration of new species of vaccines are being conducted [4–8]. Some new variants of COVID-19 have been emerging, which may exacerbate COVID-19 symptoms, while researches reveal that many still with good immunogenicity [9, 10]. However, some studies show concern on prevention efficacy in the situation [11, 12]. For this, some researchers argue for strengthening injection of current NCV; simultaneously, new NCVs are being developed by countries [13, 14]. According to the WHO, till October 5, 2021, 124 of NCV products are in clinical development, and 194 are in pre-clinical development worldwide, with the top three types of NCVs listed as protein subunit (43, 35%), viral vector (non-replicating, 18, 15%), and DNA (12, 10%) [15].

Clinical experiments observed some adverse events following immunization (AEFI) in potential association with injection of NCVs, though most of them disappeared after several or a dozen days without special medical intervention. Among them, most frequent events were localized reactions (such as pain, sore, swelling, and itching), followed by fatigue, fever (some with chills), headache, myalgia, dizziness, and nausea (some with vomiting) [4–6, 16–19]. Mechanically, most AEFI are induced by hypersensitivity of organs or immune response to vaccine, which is more obvious in strengthening injection of NCV, especially [20, 21].

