#### Strategies to improve adherence to interventions {11c}

All of the AA and SAA interventions and service will be free for the participants, and they were informed at the beginning of the trial that two sessions of AA therapy, based on individual health condition, would be provided for free upon accomplishment of the study.

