## Assignment of interventions: allocation

### Sequence generation {16a}

After confirmation for eligibility and collection of written informed consents, participants will be randomized through a random allocation software (The Hefei Big Orange Software Technology Co., Ltd, V 2.1.8), and be allocated to the AA, SAA, and WL groups in a 1:1:1 ratio with stratifying by centres.

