## Statistical methods

### Statistical methods for primary and secondary outcomes {20a}

Descriptive analyses will be made of frequencies and percentages for the qualitative variables, and overall *p* values will be estimated by *χ*^2^ or fisher *χ*^2^ test as appropriate with the Bonferroni approach. Pairwise comparisons will be performed as differences of percentages (DP), with 95% CIs of the differences calculated by R (V4.0.1). Estimations for *p* values of the pairwise comparisons will be performed by *χ*^2^, continuous or Fisher *χ*^2^ test as appropriate in SPSS (V23.0). Two-tailed tests with *p* < 0.05 define statistically significant for all analyses.

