### Methods for additional analyses (e.g. subgroup analyses) {20b}

In additional analyses, the dosage of NCVs, genders, ages, and any experience of receiving AA therapy will be determined for each treatment arm.

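### Vaccine dose number (first or second) is left out of the primary between-arm comparison; this does not bias the comparison but gives up a little precision

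*Protocol article*

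**What the plan says.** The note to Table 2 (Participant timeline {13}) defines the first time point as "T1*, immediately after the first or second dose of NCV" and words the later time points in the same way. The eligibility criteria do not restrict entry to one dose.

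Sequence generation {16a} allocates participants "in a 1:1:1 ratio with stratifying by centres". Centre is the only stratum named.

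The section on methods for primary and secondary outcomes {20a} uses chi-square or Fisher tests. It adds: "Pairwise comparisons will be performed as differences of percentages (DP), with 95% CIs of the differences". No covariate or stratum enters these comparisons.

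The section on additional analyses {20b} says "the dosage of NCVs, genders, ages, and any experience of receiving AA therapy will be determined for each treatment arm". It does not say whether dosage means dose number, and it names no model, adjustment or interaction test.

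On reactions to repeat injection, Background and rationale {6a} describes immune-driven events with the remark "which is more obvious in strengthening injection of NCV, especially". It gives no event rate by dose.

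**The concern.** The primary outcomes are the percentages of participants who report any adverse event following immunization and who report local pain at the injection site. If these percentages differ between the first and second dose, dose number is a baseline predictor of the outcome. It is known before randomisation and cheap to record. A crude comparison of percentages ignores it. The variation between doses then stays in the error term, and any chance imbalance in dose mix between arms stays in the estimate.

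What is at stake is the precision of the pairwise differences in a trial whose size was not derived from a power calculation. The listing under additional analyses does not recover that precision. A breakdown by dose gives smaller comparisons, not a more precise overall one.

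**Working it through.** There is no figure in the plan to reproduce: Sample size {14} states that no formal calculation was made. What follows is illustrative.

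**Inputs**
- From the article: at least 360 participants, 1:1:1, so n = 360/3 = 120 per arm; two-sided 5% level.
- Assumed: half of participants at each dose; the event rates by dose shown below; relative risks of 0.5 and 0.6 for the power check.

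**1. Chance imbalance in dose mix between two arms**
SD of the difference in second-dose share = sqrt(2 × 0.25/120) = 0.0645. The 95% range is ±1.96 × 0.0645 = ±12.7 percentage points. Multiplied by an assumed gap in event rate between doses:
- gap of 10 points: ±1.3 points on the between-arm difference
- gap of 20 points: ±2.5 points
- gap of 30 points: ±3.8 points

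**2. Compared with the confidence interval**
With rates of 20% and 40% by dose, the pooled rate is 30%. The 95% half-width of a pairwise difference is 1.96 × sqrt(2 × 0.21/120) = ±11.6 points. The imbalance part has variance (0.0645 × 0.20)² = 0.000167, against a total of 2 × 0.21/120 = 0.0035. That is 4.8% of the total, so it is already inside the crude interval. Removing it gives 1.96 × sqrt(2 × 0.20/120) = ±11.3 points.

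**3. Share of variance removed by adjusting for dose**
1 − (mean within-dose p(1−p)) / (pooled p(1−p)), for equal rates across arms:
- 20% and 30%: 1 − 0.185/0.1875 = 1.3%
- 20% and 40%: 1 − 0.20/0.21 = 4.8%
- 30% and 60%: 1 − 0.225/0.2475 = 9.1%
- 20% and 50% (used in the power check): 1 − 0.205/0.2275 = 9.9%

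**4. Power at 120 per arm**
Power = Φ(D/SE − 1.96), where D is the difference in percentages. The SE is unpooled. The crude SE uses the pooled rates; the stratified SE combines two equal dose strata of 60 per arm.

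Worked case: control rates 20% and 40%, relative risk 0.5, so D = 0.30 − 0.15 = 0.15. Crude SE = sqrt((0.21 + 0.1275)/120) = 0.0530, power 80.7%. Stratified SE = sqrt([(0.16 + 0.09)/60 + (0.24 + 0.16)/60]/4) = 0.0520, power 82.2%.

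| Control rates, dose 1 / dose 2 | Relative risk | Crude | Stratified | Gain (points) |
|---|---|---|---|---|
| 20% / 30% | 0.5 | 71.0% | 71.4% | 0.4 |
| 20% / 40% | 0.5 | 80.7% | 82.2% | 1.5 |
| 20% / 50% | 0.5 | 88.2% | 90.5% | 2.3 |
| 20% / 30% | 0.6 | 49.7% | 50.1% | 0.4 |
| 20% / 40% | 0.6 | 59.4% | 61.1% | 1.7 |
| 20% / 50% | 0.6 | 68.6% | 72.1% | 3.5 |

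The crude standard error is 0.5 to 4% larger than the stratified one. These figures are for a single pairwise test at 5%, without a multiplicity correction.

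**5. Why the dose subgroup is no substitute**
With 60 per arm within one dose, power for 30% against 15% falls from 79.8% to 50.3% (test with pooled variance). For 30% against 18% it falls from 58.7% to 33.5%.

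**The case against.** The strongest case against raising this is that nothing here is an error. Randomisation balances dose in expectation, stratifying by centre alone is an ordinary choice, and mixing doses fits the stated objective. The trial calls itself explorative, dosage is already listed for additional analysis, and covariate adjustment is often left to a statistical analysis plan, which is not shown. Most of this stands, and it limits the point to efficiency. It does not remove the point, because the article does state its primary method, and that method is crude when a slightly better one costs almost nothing.

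Three stronger readings are tempting, and the document does not support them.

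- A reader might infer that dose mix distorts the treatment effect. It does not do so systematically. The ±2.5 points in step 1 is an extreme chance value under assumed rates, and it already lies within an interval of about ±11.6 points.
- A reader might take the background section as establishing that the second dose causes more reactions. The same section uses the term earlier where "some researchers argue for strengthening injection of current NCV" in response to variants. It therefore most naturally means a booster, and it supports a gap between first and second dose only indirectly.
- A reader might infer that people can enter once after each dose, carry exposure over and recognise the sham points, because the exclusion on prior participation names only other trials and completers are promised "two sessions of AA therapy, based on individual health condition, would be provided for free upon accomplishment of the study". This rests on silence in a condensed article. Nothing in it provides for re-enrolment, the sample size counts participants, and completion of the study may mean the end of the whole trial. If 10% of entries were re-entries (an assumption), about 10%/3 = 3.3% of control-arm entries would have been allocated real acupressure earlier. This cannot carry a finding.

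**Conclusion.** The point holds as a modest matter of efficiency. Both doses are eligible, dose number is neither a stratum nor a term in the primary comparison, and it appears only under an ambiguous label in the additional analyses. The randomised comparison remains unbiased.

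The loss from ignoring dose is about 1 to 9% of the variance (9.9% for 20% against 50%), or roughly 0.4 to 3.5 percentage points of power. These sizes rest on 120 per arm, an even dose mix, and assumed event rates and relative risks. If reaction rates do not differ by dose, the loss is essentially nil. It is an inexpensive improvement to the stated method, and it does not threaten the trial's conclusions.

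**What to change.** - In the additional analyses {20b}, define dosage as dose number, first or second.
- In the primary analysis {20a}, stratify or adjust the pairwise differences of percentages for dose number together with centre, for example with a Mantel-Haenszel risk difference and its 95% confidence interval. Four centres and two doses give 8 strata, about 360/(8 × 3) = 15 per arm in each if evenly spread. The Mantel-Haenszel estimate is suited to strata of that size.
- Keep the dose subgroup as a secondary analysis.

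The cost is slightly more analysis work, and the randomisation need not change.

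As an optional clarification only: confirm that each person is randomised once, and say when the free acupressure sessions are given.

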### Sample size {14}

No less than 360 participants will be randomized in 1:1:1 ratio to each group. This is a protocol for an explorative study; therefore, a formal sample size is unavailable and not calculated.

### Recruitment {15}

We will recruit participants through leaflets and posters when waiting for the injection, and will be advertised, recruited during remaining in the medical institutions for post-injection observation (at less 30 min). Trial investigators will examine respondents in the observation areas for eligibility screening.

## Assignment of interventions: allocation

### Sequence generation {16a}

After confirmation for eligibility and collection of written informed consents, participants will be randomized through a random allocation software (The Hefei Big Orange Software Technology Co., Ltd, V 2.1.8), and be allocated to the AA, SAA, and WL groups in a 1:1:1 ratio with stratifying by centres.

### Concealment mechanism {16b}

Sequentially numbered sequences with combination of numbers and letters will be performed and recorded by registrars to conceal the random sequence for the participants, outcome assessors, and statisticians.

### Implementation {16c}

The sequences will be generated and concealed by trained research assistants.

## Assignment of interventions: blinding

### Who will be blinded {17a}

The participants in the AA group and SAA group, outcome assessors, and statisticians will be blinded, while participants in the WL group and the acupuncturists will not.

### Procedure for unblinding if needed {17b}

As for procedure for unblinding, the research assistants will record, unblind, and state it through the registration system if it is needed.

## Data collection and management

### Plans for assessment and collection of outcomes {18a}

In addition to the primary and secondary outcomes in our protocol, AEFI with extra specific medical intervention will be recorded. Adverse events associate with the AA therapy for AA and SAA groups will also be recorded, with cases, severity, measurement, and outcomes. Follow-ups will be performed by trained and blinded evaluators at baseline and 1, 3, 5, 7, and 14 days after the injection. However, due to the large number of vaccinations in facilities, especially in the waiting and observation areas, time-consuming questionnaires and indicators with more complexity will not be implemented. Data will be collected by a specialized research assistant, who will be responsible for the patient consents and case report forms.

### Plans to promote participant retention and complete follow-up {18b}

Participants who discontinue or deviate from the intervention protocols will be connected online or by phone, with their reasons for discontinue or deviate recorded. They will still be encouraged to report the AEFI in themselves during follow-ups and be told that two sessions of free AA therapy, based on individual health condition, would be provided for free upon accomplishment of the study

### Data management {19}

Data will be entered electronically in our study with double entry and range checks by trained and blinded researchers and will be recorded with good security. Soft copies of the research materials will be saved on a storage device, and all data will be maintained in a locked storage and only those with permission from the principal investigators will be able to access the data. All the retained data will be coded to identify the patients instead of personal information. The principal investigators will be given access to the cleaned datasets. In order to ensure confidentiality, the project team members will be blinded to any identifying participant information.

### Confidentiality {27}

During and after the trial, personal information about potential and enrolled participants will be kept in a pre-designated researcher of our study with good confidentiality. Data collected during the course of the research will be kept strictly confidential and only accessed by members of the trial team. Participants will be allocated an individual trial identification number when their details are stored on a secure database.

### Plans for collection, laboratory evaluation, and storage of biological specimens for genetic or molecular analysis in this trial/future use {33}

No biological sample will be collected in our study.

## Statistical methods

### Statistical methods for primary and secondary outcomes {20a}

Descriptive analyses will be made of frequencies and percentages for the qualitative variables, and overall *p* values will be estimated by *χ*^2^ or fisher *χ*^2^ test as appropriate with the Bonferroni approach. Pairwise comparisons will be performed as differences of percentages (DP), with 95% CIs of the differences calculated by R (V4.0.1). Estimations for *p* values of the pairwise comparisons will be performed by *χ*^2^, continuous or Fisher *χ*^2^ test as appropriate in SPSS (V23.0). Two-tailed tests with *p* < 0.05 define statistically significant for all analyses.

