## Methods: participants, interventions, and outcomes

### Study setting {9}

This study is approved by the Ethics Committee of Hospital of Chengdu University of Traditional Chinese Medicine (2021KL-015), and jointly funded. No less than 360 participants for one type of NCV will be advertised and enrolled and randomly assigned to one of the three groups. Participants will be advertised and enrolled in four centres in Chengdu, China, including Hospital of Chengdu university of Traditional Chinese Medicine, Caotang Community Health Service Center, Xi’an Road Community Health Service Center, and Wenjiang School Hospital of Chengdu University of Traditional Chinese Medicine. To examine the effectiveness of AA therapy in preventing and (or) relieving AEFI related to NCV, measurements will be taken once the injection is completed, and the participants will be followed after 1, 3, 5, 7, and 14 days after NCV injection. Participants will be asked to accept assessments at baseline. This randomized controlled clinical trial began recruitment on March 17, 2021, and the anticipated completion date is February 2022. The primary outcome are quality and quantity evaluation among participants who reported any AEFI and who reported local pain at injection site. The flow chart of the trial is shown in Fig. 1. Informed consent is obtained from each participant. The protocol is reported following the *Trials* structured template [30].

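### Allocation is stratified by centre, but the named tests ignore centre; the cost is conservative and probably small unless AEFI rates differ strongly between centres

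*Protocol article*

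**What the plan says.** Sequence generation {16a} states that participants will "be allocated to the AA, SAA, and WL groups in a 1:1:1 ratio with stratifying by centres". Study setting {9} says "Participants will be advertised and enrolled in four centres in Chengdu, China" and lists a university hospital, two community health centres and a university campus hospital. No blocking within centre is mentioned.

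The primary outcomes are binary: the share of participants with any AEFI and the share with injection-site pain (Outcomes {12}). For these, Statistical methods {20a} fixes the pairwise p values as chi-square, continuity-corrected or Fisher tests in SPSS, two-sided at 5%. On estimation it says "Pairwise comparisons will be performed as differences of percentages (DP), with 95% CIs of the differences calculated by R (V4.0.1"; the interval formula is not named.

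Centre is not among the factors for additional analysis in {20b}, where "the dosage of NCVs, genders, ages, and any experience of receiving AA therapy will be determined for each treatment arm". On size, Sample size {14} says "No less than 360 participants will be randomized in 1:1:1 ratio to each group" and that "a formal sample size is unavailable and not calculated". No expected AEFI rate is given, overall or by centre.

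**The concern.** Stratified allocation that is balanced within centre removes differences between centres from the treatment contrast. A pooled chi-square test and a crude standard error do not know this, and still count the variation between centres as random error. The reported standard error is then larger than the true one: the test rejects less often than 5% under the null, and the interval covers more than 95%. An analysis stratified by centre recovers that loss.

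The point is not a detail left to an unseen analysis plan. Section {20a} names the tests and the software, and the tests it names do not follow the randomisation. At stake is some precision and power, not protection against false positives.

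**Working it through.** There is no stated power or precision figure to reproduce, because {14} says none was calculated.

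**Inputs from the article:** four centres ({9}); at least 360 participants 1:1:1, so 360/3 = 120 per arm and 240 per pairwise comparison ({14}); two-sided 5% ({20a}).

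**Inputs assumed, because the article gives none:** equal centre sizes, centre-specific AEFI rates, and a 15-point reduction in every centre.

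**Step 1, formula under the null with exact balance within centre.** Let p_c be the rate in centre c and p̄ the mean rate.

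- True variance of the difference / crude variance = V = mean[p_c(1 − p_c)] / [p̄(1 − p̄)].
- Crude SE / true SE = 1/√V.
- Actual type I error of the crude test = 2Φ(−1.96/√V).

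| Assumed centre rates | Numerator | Denominator | V | SE ratio | Type I error |
|---|---|---|---|---|---|
| 30/35/40/45% | 0.23125 | 0.234375 | 0.987 | 1.007 | 4.8% |
| 20/30/40/50% | 0.215 | 0.2275 | 0.945 | 1.029 | 4.4% |
| 15/25/40/60% | 0.19875 | 0.2275 | 0.8736 | 1.070 | 3.6% |

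For the last row, the numerator is (0.1275 + 0.1875 + 0.24 + 0.24)/4 = 0.19875 and the denominator is 0.35 × 0.65 = 0.2275.

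**Step 2, simulation with allocation balanced within centre.** There were 100,000 runs per scenario, 120 against 120 in four equal centres, with a mean control rate of about 40%. The crude method is the uncorrected chi-square test with a Wald interval. The stratified method is the CMH test with a Mantel-Haenszel-weighted risk difference. As a check, the closed-form power for 40% against 25% with 120 per arm is 70.1%, which matches the first row. Type I error is under no effect; the other columns are under the 15-point effect.

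| Range of centre rates | Type I error, crude | Power, crude → CMH | CI half-width (points), crude → stratified | Width ratio | Coverage, crude |
|---|---|---|---|---|---|
| none (all 40%) | 5.17% | 70.1 → 70.2% | 11.65 → 11.69 | 1.00 | 94.8% |
| 35–45% | 5.05% | 70.1 → 70.4% | 11.65 → 11.65 | 1.00 | 94.8% |
| 30–50% | 5.01% | 70.5 → 71.5% | 11.65 → 11.54 | 1.01 | 95.2% |
| 20–60% | 4.18% | 70.8 → 74.9% | 11.65 → 11.06 | 1.05 | 96.0% |
| 16–80% (extreme) | 2.57% | 72.9 → 83.9% | 11.69 → 9.94 | 1.18 | 97.7% |

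**Step 3, the same scenarios with simple, unblocked allocation within centre.** The crude test keeps a type I error of 5.0 to 5.1% and a coverage of about 94.7 to 94.8% throughout, so the crude interval is not too wide for its design. Power, crude → CMH, in the same order of rows, is 70.3 → 69.6%, 70.2 → 69.8%, 70.1 → 70.6%, 70.2 → 74.3% and 70.2 → 83.2%. Stratifying costs at most 0.7 point when centres are alike and gains about 4 points at a 40-point spread.

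**The case against.** A reader might infer that the intervals are certainly too wide and that power is certainly given away. The article does not support that. The loss needs event rates that differ between centres, and excess width also needs close balance within centre. No rates are given and no blocking is described. All four centres are in one city and share the same eligibility criteria, so a spread as wide as 15 to 60% has no basis in the text. This stands, and it limits how large the point can be.

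The crude interval is partly an inference. The tests are explicitly unstratified, but for the CI only the software is named. This also stands. If the interval were in fact stratified, though, it would sit beside a crude p value and the two could disagree, so the wording would still need settling.

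The trial is declared explorative and has no power target, so no stated figure is breached. With exact balance the crude and Mantel-Haenszel risk differences are the same number, and only the reported uncertainty changes. Both are true. They make the point minor without removing it.

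A reader might go further and ask for adjustment for dose number, vaccine type, age and sex, or for interaction tests. The documents do not carry that as part of this point. Such adjustment does not follow from stratifying by centre, and its gain cannot be sized from the article. Vaccine type is not listed in {20b} and may not vary, since {9} sets the 360 per type of vaccine. The Background remark that reactions are stronger, "which is more obvious in strengthening injection of NCV, especially", appears to concern boosters, whereas the participant timeline concerns the first or second dose.

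**Conclusion.** The mismatch is real: centre is the stratification factor in {16a} and appears in no analysis in {20a} or {20b}. Its consequence is conditional. With balance within centre and the assumed rates, the effect is negligible to small for centre spreads up to about 20 points (interval 0 to 1% wider, about 1 power point or less). It becomes material at about 40 points (interval about 5% wider, about 4 power points). Any error is conservative, so type I error is not inflated and the validity of the trial is not in question. These sizes rest on equal centre sizes, 120 per arm, a mean control rate near 40% and a 15-point effect, none of which except the arm size comes from the article. Severity: minor.

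**What to change.** In {20a}, make the primary pairwise comparisons a Mantel-Haenszel risk difference stratified by centre, with its 95% CI, and a Cochran-Mantel-Haenszel test stratified by centre. Name the interval method so that the estimate and p value rest on the same analysis. Keep the crude chi-square or Fisher analysis for sparse outcomes, or as a sensitivity analysis. If the sponsor prefers the crude analysis as primary, {20a} should say why.

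The cost is wording only. Centre is known for every participant from the allocation, so no new data, visits or participants are needed. In the simulations, the price of stratifying when centres turn out alike was at most about 0.7 power point.

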**Methods:**

The study design is a randomized, multicentre, three-arm controlled, single-blind trial. Participants meeting the inclusion criteria will be advertised and enrolled and assigned in the medical institutions randomly for post-injection observation. No less than 360 participants will be randomized into one of three groups: auricular acupressure group, sham auricular acupressure group, and wait-list group. Interventions will be performed immediately and will happen 4 to 5 times per day for 5 days. The primary clinical outcomes will be quality and quantity evaluation among participants who reported any AEFI and who reported local pain at injection site. Secondary outcomes will concern headache, muscle and (or) joint pain, fatigue, nausea, vomiting, diarrhoea, and other potential events. All the outcomes will be assessed at baseline and 1, 3, 5, 7, and 14 days after the injection. Both intention-to-treat and per-protocol analyses will be performed, with significance level determined as 5%.

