### Outcomes {12}

All outcomes will be accessed and evaluated from the participants online or by phone in 1, 3, 5, 7, and 14 days after NCV injection, which they thought might be related to the injection. Primary outcomes are percentages of participants who reported any AEFI and who reported local pain at injection site, with their severity evaluated by visual analogue scale (VAS) scores of 0–10. Secondary outcomes include percentages of participants who reported headache, muscle and (or) joint pain, fatigue, nausea, vomiting, and diarrhoea, together with other AEFI reported by participants but not listed above, and with their severity evaluated by the VAS scores, similarly.

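### Bonferroni is attached to the three-arm overall tests, while the pairwise AA contrasts are read at an uncorrected 0.05, so error in AA's favour is well above nominal

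*Protocol article*

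**What the plan says.** All of this is in the Protocol article.

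- **Overall tests.** Section {20a} obtains overall p values by a chi-square or Fisher "test as appropriate with the Bonferroni approach". The number of tests that the correction covers is not given.
- **Pairwise tests.** The next sentence reads "Pairwise comparisons will be performed as differences of percentages (DP), with 95% CIs of the differences calculated by R (V4.0.1"). Pairwise p values then come from chi-square, continuity-corrected or Fisher tests. Neither sentence mentions an adjustment or makes these tests depend on the overall result.
- **Threshold.** The section ends with two-tailed p < "0.05 define statistically significant for all analyses". The abstract also gives a 5% level.
- **Outcomes and times.** Outcomes {12}: "Primary outcomes are percentages of participants who reported any AEFI and who reported local pain at injection site", each with a VAS severity score. Study setting {9}: "the participants will be followed after 1, 3, 5, 7, and 14 days after NCV injection".
- **Contrasts.** Objectives {7} sets AA against both sham (SAA) and wait-list (WL).
- **Blinding.** AA and SAA participants are blinded, "while participants in the WL group and the acupuncturists will not" (section {17a}).
- **Status.** Trial design {8}, Sample size {14} and the Discussion call the study explorative.

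**The concern.** A claim that AA prevents or relieves adverse events would rest on AA versus SAA or AA versus WL, not on a three-arm overall test. As written, the correction falls on the overall test and the contrasts that carry the claim have none. One favourable day on one outcome against one control would meet the plan's definition of statistical significance.

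The overall test is also a poor shield for the blinded contrast. WL participants know that they are untreated, and they report events that they themselves attribute to the injection. If they report more, the overall test can be significant with AA and SAA identical. Ten AA-versus-SAA tests at 0.05 would then follow.

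**Working it through.** The plan has no derived error rate or power to reproduce: section {14} states that the sample size was not calculated. The 5% level agrees between the abstract and {20a}.

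**Inputs from the protocol.** Two primary percentages; five days (1, 3, 5, 7, 14); three arms at 1:1:1, so three contrasts, two of them involving AA; at least 360 participants, read as 360/3 = 120 per arm; two-tailed 0.05.

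**Count of tests.**
- All pairwise: 2 x 5 x 3 = 30.
- Involving AA: 2 x 5 x 2 = 20.
- AA versus SAA: 2 x 5 x 1 = 10.

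VAS severity, the per-protocol repeat and the secondary outcomes would add to these.

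**If the tests were independent and no arm differed.**
- Any false positive in 30: 1 - 0.95^30 = 78.5%.
- Any false AA contrast, either direction: 1 - 0.95^20 = 64.2%.
- A false result in AA's favour: 1 - 0.975^20 = 39.7%.

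The last line uses 0.025 because only half of the two-sided error favours AA.

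**Allowing for correlation.** Days, outcomes and contrasts sharing an arm are correlated, so the global null was simulated with 120 per arm. Event rates and correlations are assumptions; the protocol gives none.

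- *Set A:* pooled two-proportion tests; rates flat (30% and 20%) or falling (40% to 6% and 30% to 3%); latent correlation 0 to 0.95 between days and 0 to 0.9 between outcomes.
- *Set B:* local pain 40/20/8/4/2% and any event 55/35/15/8/5% on the five days, pain nested in any event; latent day-to-day correlation 0.3 to 0.8; chi-square, or Fisher when expected counts are below 5.

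| At least one p < 0.05 | Set A | Set B |
|---|---|---|
| Any of 30 | 43-73% | 56-62% |
| In AA's favour, 20 AA tests | 18-37% | 24-28% |
| AA better than SAA, 10 tests | 11-22% | 14-17% |

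Against the 2.5% of a single test, 18% to 39.7% in AA's favour is 18/2.5 = 7 to 39.7/2.5 = 16 times.

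**If a gate was meant.** Suppose pairwise tests are read only after an overall test at 0.05/10 = 0.005 (the divisor is an assumption).
- All arms equal, Set A: any false positive 2.7-5.0%; in AA's favour 1.3-2.5%.
- All arms equal, Set B: a false AA-versus-SAA result in either direction, about 2%.
- AA = SAA, WL reporting inflated 1.3 to 1.6 fold (assumed), Set B: a false AA-versus-SAA result in either direction, about 8-17%; in AA's favour, 4-9%.

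**If Bonferroni was meant only for the three contrasts within each outcome and day** (0.05/3 = 0.0167): Set A still gives 19-36% for any false positive and 7-15% in AA's favour.

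**The case against.** - **Ambiguity.** Bonferroni is named just before the pairwise comparisons, so it may be meant for them, or the overall tests may be meant as a gate. Adjusted p values judged against 0.05 would also fit the closing sentence. This stands as a reason for moderation. It does not clear the text: no family is given, and correcting only the three contrasts within each outcome and day leaves the error high.
- **Explorative status.** No sample size was calculated for this reason, and the Discussion presents larger studies as the next step. This lowers the severity. It does not remove the problem, because the objective is to test effectiveness, the Discussion expects a basis for effectiveness, and significance is defined for every analysis.
- **Detail for an analysis plan.** A primary day, the order of contrasts and the divisor are commonly settled there, and neither an analysis plan nor the full Chinese protocol is shown. This also stands: their absence is not the point. The point is that the multiplicity rule that is printed covers the wrong tests.
- **Stronger reading.** A reader might infer that a false claim for AA is likely. The figures do not support that. The 43-79% range counts both directions and includes ten SAA-versus-WL tests that cannot support AA. In AA's favour the chance stays below one half, and against sham it is 11-22%.

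**Conclusion.** The concern holds in a limited form, as something that should be fixed. Read as written, {20a} corrects the overall tests and leaves the pairwise AA contrasts uncorrected. With no true effect this gives a roughly 20-40% chance of at least one false result in AA's favour, and roughly 45-75% for any false positive among the 30 tests. These figures rest on 120 per arm, assumed event rates and correlations, and no gate; they exclude VAS severity, per-protocol and secondary analyses. Under an unstated Bonferroni gate the error is controlled when all arms are equal. What remains then is the blinded contrast, at about 8-17% in either direction if wait-list reporting is inflated as assumed.

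**What to change.** Reword {20a} before unblinding, in one of two ways.

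1. **Keep significance testing.** Name a primary time point, or a single summary over follow-up, for each primary outcome. Apply Bonferroni or Holm to the pairwise AA contrasts over a stated family. For example, two outcomes by two AA contrasts is four tests at 0.05/4 = 0.0125, with family-wise error at most 5% (1 - 0.9875^4 = 4.9% if independent). If all five days are kept, the family is 20 tests at 0.05/20 = 0.0025. Report other days, SAA versus WL, per-protocol and secondary outcomes as estimates with 95% CIs and no significance claim. If the overall test is a gate, say so and give its divisor, but still correct the AA contrasts.
2. **Follow the explorative label.** Delete the rule that defines significance for all analyses, and report every pairwise result as an exploratory estimate with its CI.

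Testing AA versus WL only after AA versus SAA succeeds is an option, not a required correction.

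Cost: no extra participants or visits. Under the first option fewer results can be called significant and power per contrast falls; under the second, none can. Recruitment began in March 2021, so the change should be dated and documented as made without sight of unblinded data.
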